### Clinical Assessments

A schedule of assessments and measurements is presented in Table 1.

**Table 1 table1:** Summary of study activities.

	Visit 1 (20, SD 4 weeks gestation)	Visit 2 (36, SD 4 weeks gestation)	Visit 3 (Peripartum)	Visit 4 (12-18 months postpartum)
Informed consent and eligibility	✓	✓		
Collect basic demographic details including postcode	✓			
Collect past medical, surgical, obstetric, and gynecological	✓			
Collect new medical, surgical, obstetric, and gynecological		✓	✓	✓
Adverse events		✓	✓	✓
Medication	✓	✓	✓	✓
Allergies	✓	✓	✓	✓
Smoking, drug, and alcohol use history	✓			
Maternal Anthropometry				
Height	✓			
Weight	✓	✓		✓
Waist circumference	✓	✓		✓
Bioimpedance	✓	✓		✓
Blood tests				
Glucose, insulin, and c-peptide	✓	✓		✓
HbA_1c_^a^	✓	✓		✓
CRP^b^	✓	✓		✓
Leptin	✓	✓		✓
Provide maternal and neonatal mouth swabs to participants		✓		
Collect 75g OGTT^c^ result		✓		✓
Collect obstetric ultrasound results		✓		
Collect maternal and neonatal mouth swabs for epigenetic analysis		✓	✓	
Collect obstetric medical records including the birth summary		✓	✓	
Collect height and weight data from the childhood development book (“Baby book”)		✓		✓

^a^HbA_1c_: hemoglobin A_1c_.

^b^CRP: C-reactive protein.

^c^OGTT: oral glucose tolerance test.

#### Medical History and Medications

At the first visit, a full medical history will be taken by a trained clinician including past medical history and surgical history. Outcomes of previous pregnancies will be recorded including outcome of the pregnancy, gestation, pregnancy complications, and (if relevant) birthweight and neonatal complications. Current medications including dose, and dosing schedule will be recorded. Smoking, alcohol, and recreational drug use will be recorded.

#### Blood Pressure

Blood pressure will be measured after 5 minutes of rest in a seated position using an appropriately sized cuff on the bared left upper arm supported at heart level. Auscultatory readings with an aneroid sphygmomanometer and stethoscope or automated oscillometric readings with a single read per activation device will be collected by trained operators**.**

#### Weight, Height, and Waist Circumference

Weight will be measured by a trained technician on calibrated digital scales with an accuracy of ±0.01 kg. Participants will be asked to wear light clothing but no shoes. Height will be measured by a trained technician using a standing stadiometer with an accuracy of ±0.5 cm. Waist circumference will be measured with an accuracy of ±0.5 cm using a standard tape measure according to the WHO guidelines (at the end of a normal expiration, at the midpoint between the lower margin of the last palpable rib and the top of the iliac crest, as the average of 2 measurements). BMI will be calculated by dividing weight in kg by height in meters squared.

#### Bioimpedance Analysis

Bioimpedance will be performed using the DC-430MAS Tanita Dual Frequency Body Composition Analyser. Data obtained from bioimpedance analysis will include fat mass (%), fat mass (kg), free fat mass (kg), muscle mass (kg), and bone mass (kg).

#### Laboratory Assays

Phlebotomy is a low-risk procedure. At each visit, the required blood samples will be taken for glucose, insulin, C-peptide, high-sensitivity C-reactive protein, and leptin using an aseptic technique. Samples will be mixed by inversion and centrifuged at 4 °C. Plasma from the tubes will be aliquoted into 5 microtubes with 2 spare microtube samples. Plasma samples will be batched for analysis to minimize interassay error. The sample will be stored at –80 °C before analysis. Spare tubes will only be used in the event of a processing error.

Samples will be tested by commercial laboratories accredited by the National Association of Testing Authorities (Australia) and The Royal College of Pathologists of Australia for compliance with National Pathology Accreditation Advisory Council (Australia) standards and ISO (International Organization for Standardization) 15189. Test results were interpreted in accordance with normative reference values. The study database allows the management of the samples.

#### Calculated Insulin Resistance

Homeostasis model assessment of insulin resistance (HOMA-IR) values will be calculated by the equation (fasting insulin [μU/mL] × fasting glucose [mM])/22.5. Insulin resistance is defined by a HOMA value >4 (reference).

#### Oral Glucose Tolerance Test Results and Other Forms of Testing for Gestational Diabetes

The 75-g oral glucose tolerance test (OGTT) is a standard of care to screen for GDM at 24-28 weeks’ gestation in Australia. A 75-g OGTT may also be performed at 10-20 weeks of gestation if there are risk factors for GDM. A diagnosis of GDM may also be made using other methods such as HbA_1c_ (hemoglobin A_1c_), glucose readings from a period of fingerstick monitoring, or by evaluating continuous glucose monitoring CGM) metrics. If the woman is considered to have GDM by the treating clinical team, she will also be given this diagnosis for the purpose of the study. All medications used to treat GDM will be recorded.

For all such women, a 75-g OGTT or some other form of testing for diabetes should be repeated >6 weeks’ post partum and these results will also be collected.

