### Recruitment Procedure

Women will be recruited when they attend maternity care visits between 16 and 24 weeks’ gestation. Initial contact will be made by the maternity care provider. Subsequent contact will be made by a dedicated study nurse/doctor at the time of the standard maternity care visit. All participants will receive standard individualized antenatal care based on their clinical needs.

No study activities will be performed before eligibility has been assessed and informed consent has been formally documented. To encourage attendance at clinical visits, parking and meal vouchers will be provided. At the final visit, women will be provided with a comprehensive summary of their metabolic health and a plan for appropriate long-term follow-up.

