#### Secondary Outcomes

A composite of adverse neonatal outcomes includes the following:

Offspring with birthweight ≥90th centile on population-based charts (LGA).Offspring with birthweight ≤10th centile on population-based charts (SGA).Offspring with major congenital abnormalities.Offspring born preterm (<37 completed weeks’ gestation).

A composite of new maternal metabolic disease that develops during pregnancy or <18 months postpartum is defined below:

Gestational diabetes (GDM) as per the International Association of the Diabetes and Pregnancy Study Group (IADPSG)/World Health Organization (WHO) definition (reference); or diabetes in pregnancy as per WHO/IADPSG definition; or previously undiagnosed type 2 diabetes as per American Diabetes Association/WHO definition; or prediabetes as per American Diabetes Association definition (Table S1 in Multimedia Appendix 1).Gestational hypertension; or pre-eclampsia; or eclampsia; or new essential hypertension after pregnancy (Table S2 in Multimedia Appendix 1).Gestational weight gain ≥20 kg or new overweight/obesity after pregnancy (BMI ≥25 kg/m^2^ and body weight increase of ≥5 kg compared with prepregnancy weight) at the 12-18 months postpartum visit.

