### Statistical Methods

This study will follow the Transparent Reporting of a Multivariable Prediction Model for Individual Prognosis or Diagnosis reporting guidelines for prognostic studies [14]. Summary characteristics of the study cohort will be described using means (with SD) or medians (with IQRs) for continuous variables, depending on the shape of the distribution, and numbers and percentages for categorical variables.

A risk calculator will be developed to determine the risk of an abnormally grown fetus (ie, the primary outcome of the study). Participant data will be split randomly into either training (70%) or validation (30%) datasets according to standard prediction model methods. Multivariable logistic regression analysis will be conducted to identify candidate predictors of poor pregnancy outcomes due to metabolic disease. After starting with the most comprehensive model that includes all potential risk factors for an LGA or SGA offspring (ie, the primary outcome). These include categorical variables including maternal SES (based on postcode), maternal parity, maternal smoking status, maternal obesity class, maternal preexisting diabetes, maternal preexisting renal disease, essential hypertension, use of antihypertensive medication, use of metformin, gestational hypertension, preeclampsia/eclampsia, previous LGA/SGA offspring, major congenital anomaly, and continuous variables including maternal age, maternal gestational weight gain, maternal glycemic control (HbA_1c_), total daily dose insulin, maternal systolic blood pressure, maternal diastolic blood pressure, birthweight of previous offspring, fasting glucose, plasma insulin, plasma C-peptide, plasma leptin, HOMA-IR.

A backward selection method will be performed to determine which combination of risk factors generates the most parsimonious predictive model. The number of candidate variables will be limited to data collected in the dataset. From this parsimonious model, model coefficients and the associated 95% CIs will be extracted to derive the risk score for predicting the delivery of LGA/SGA offspring. Internal validation of the model will be performed using 5-fold cross-validation and bootstrap validation. The performance of the model will be assessed using the AUC and calibration slope.

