A similar approach will be taken for the secondary outcomes, and these models will be used to develop risk calculators for a composite of neonatal adverse outcomes and a composite of maternal adverse outcomes. Ongoing statistical input will be provided by the University of Melbourne.

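### The maternal model does not separate gestational diabetes already diagnosed at Visit 1, so its treatment may enter as a predictor of it

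*Protocol article*

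**What the plan says.** **Outcome.** Secondary Outcomes introduces the maternal endpoint thus: "A composite of new maternal metabolic disease that develops during pregnancy or <18 months postpartum is defined below". GDM is one of its components, and the window opens with pregnancy, not with study entry.

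**Diagnosis.** The section on the oral glucose tolerance test (OGTT) says that the 75-g test "is a standard of care to screen for GDM at 24-28 weeks’ gestation in Australia", and adds: "A 75-g OGTT may also be performed at 10-20 weeks of gestation if there are risk factors for GDM". HbA1c, fingerstick or continuous glucose readings may also establish the diagnosis, with no timing given. Where the treating team considers a woman to have GDM, "she will also be given this diagnosis for the purpose of the study".

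**Predictors.** Recruitment Procedure states: "Women will be recruited when they attend maternity care visits between 16 and 24 weeks’ gestation". It also states: "No study activities will be performed before eligibility has been assessed and informed consent has been formally documented". Table 1 places the first bloods, weight and medication record at Visit 1. The inclusion criteria admit women on any medication.

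**Model.** In Statistical Methods, the categorical candidates for the primary outcome include "use of antihypertensive medication, use of metformin, gestational hypertension, preeclampsia/eclampsia". The continuous candidates include HbA1c, total daily insulin dose, fasting glucose, plasma insulin, C-peptide and HOMA-IR. For the maternal and neonatal composites the section says: "A similar approach will be taken for the secondary outcomes".

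**The concern.** A prediction model needs its predictors measured before the outcome. Here a woman at raised risk can be tested, diagnosed and treated before Visit 1 and still count as a new maternal event. Her Visit 1 glucose, insulin and HbA1c are then post-diagnosis values, and metformin or insulin may be on her record because of the diagnosis. No text in the article separates such women.

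If those variables are candidates for the maternal model, backward selection will tend to keep the treatment variables, because they partly record the outcome. Apparent discrimination rises for a reason that has nothing to do with prediction, and the glycaemic coefficients are distorted by treatment. Cross-validation and bootstrap resample the same women with the same ordering of events, so they reproduce the fault instead of revealing it.

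This matters because the Introduction and Conclusions describe a calculator that works from the mother's phenotype before pregnancy and is used for preconception triage. At that point nobody is on treatment for GDM of the coming pregnancy.

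**Working it through.** **1. The plan's own event count.** Sample Size gives 475 analysable women, about 15% developing diabetes and about 20% with any maternal metabolic disease, printed as n=90.

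- 475 × 0.20 = 95, not 90. A base of 450 gives 450 × 0.20 = 90, and the stated minimum sample of 440 gives 88.
- The figure is marked approximate and nothing here depends on it, so I carry 90-95.
- Diabetes: 475 × 0.15 = 71.25, about 71 women.

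**2. The two clocks side by side.**

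| Event | Gestation | Who |
|---|---|---|
| Early OGTT | 10-20 weeks | women with risk factors, optional |
| Visit 1, first predictors | 16-24 weeks | all participants |
| Routine OGTT | 24-28 weeks | all, as standard care |

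Tests at 10-16 weeks always precede Visit 1. Tests at 16-20 weeks may fall on either side of it.

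**3. Share of early tests that precede Visit 1.** Assume both times are uniform over their windows and independent. The chance that the early test comes after Visit 1 is the integral of (1/8) × (20 − v)/10 for v from 16 to 20, which is (1/80) × 8 = 0.10. So about 90% of early tests come first. For a fixed Visit 1 the share is 60% at 16 weeks, 80% at 18 weeks and 100% from 20 weeks.

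**4. Events that predate the predictors.** The article does not give the share of GDM found by the early test, so 10-50% is an assumption. Number = 71.25 × share × 0.9.

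| Assumed early share | Found early | Before Visit 1 | Of 95 events | Of 90 events | Events left (from 95 / from 90) |
|---|---|---|---|---|---|
| 10% | 7.1 | 6.4 | 7% | 7% | 89 / 84 |
| 20% | 14.2 | 12.8 | 14% | 14% | 82 / 77 |
| 30% | 21.4 | 19.2 | 20% | 21% | 76 / 71 |
| 50% | 35.6 | 32.1 | 34% | 36% | 63 / 58 |

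This treats the whole 15% as GDM. If it also covers diabetes first found after birth, the counts are lower in proportion.

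**5. From timing to bias.** A woman in the third column is an event with certainty when her predictors are taken. If she has started metformin or insulin for GDM, that variable marks her as an event. No figure for the resulting rise in AUC can be derived, because the article gives no treatment rates.

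**The case against.** The strongest reply is that the key step is inferred. The candidate list is presented as risk factors for abnormal birthweight, and the maternal model is described only as following a similar approach. The list contains gestational hypertension and preeclampsia, which are themselves components of the maternal composite, so a literal carry-over is doubtful. Predictor sets for secondary models are often left to the analysis plan, and the article does not name the visit that supplies the predictors. All this stands, so the point about treatment is conditional on the carry-over. The timing problem is not: the outcome window, the diagnosis rule and the visit schedule are all fixed in the article.

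The Limitations section discloses recruitment at 20±4 weeks and argues that early-pregnancy measurements track prepregnancy ones. That argument concerns anthropometry and biomarkers. It does not cover drugs started for GDM.

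Three stronger readings are tempting, and the document does not support them:

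- A reader might infer that women without risk factors escape GDM testing. They do not: the 24-28 week test is standard care, so the fault is one of timing and not of missing verification.
- A reader might infer that every early diagnosis precedes Visit 1. The windows overlap at 16-20 weeks.
- A reader might try to put a spurious odds ratio on metformin or insulin use. That needs the treated share, the background use and the true effect, none of which the article gives. It also needs a combined binary drug variable that is not on the list, where insulin enters as a continuous dose.

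**Conclusion.** The point holds in a limited form. As written, the plan lets some women be maternal outcome events, possibly under treatment, before any predictor is measured. If the listed metformin, insulin and glycaemic candidates are reused for the maternal model, GDM treatment can predict GDM and the apparent AUC will be too high.

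The size is uncertain: roughly 6 to 32 of about 90-95 maternal events. This rests on an assumed 10-50% early-diagnosis share, uniform timing, and the plan's 15% diabetes rate read as GDM. Visit 1 is the most favourable reading of when predictors are taken; values from Visit 2 (36±4 weeks) would make the problem larger.

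Only this secondary model is affected. Birthweight outside the 10th to 90th centile is not compromised as an outcome. The article reports that no analysis has been done, so the matter can still be settled beforehand.

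**What to change.** For the maternal model only:

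1. Name Visit 1 as the time point for the predictors.
2. Record the date of GDM diagnosis and the start dates of metformin and insulin. The medical history section mentions current drugs, dose and schedule, but not start dates.
3. Do not count drugs started for GDM in this pregnancy as predictors.
4. Fit the model in women without diagnosed GDM at Visit 1, or at least report its AUC and calibration slope in them.
5. Use the same predictor source for every woman. In particular, do not substitute the early OGTT value only for women already diagnosed. That would choose the source by outcome status, might use the diagnostic test itself as a predictor, and would leave gaps in the other markers that identify the events. Table 1 also lists OGTT collection only at Visits 2 and 4.

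The cost is one or two extra date fields, and 402 women had been recruited at manuscript submission, so some dates may have to be recovered from hospital records. The restricted analysis has fewer events, about 63-89 instead of 95 (58-84 instead of 90) under the assumptions above, and its apparent AUC is likely to be lower. No change to clinical testing or treatment is implied.

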#### Obstetric Ultrasound

Obstetric ultrasounds are routinely performed in Australia to assess fetal morphology at 20-22 weeks’ gestation. The fetal morphology scan report will be collected from all participants. Fetal growth scans may be performed at 28, 32, or 36 weeks for obstetric indications. If growth scans are performed, the estimated fetal weight and abdominal circumference will be collected from ultrasounds that have been formally reported. The reported customized growth centiles are based on GROW customized charts which are customized for known constitutional variables (maternal height, weight, ethnic origin, and parity) but not pathological factors such as smoking and diabetes. This method of customization has been demonstrated to classify the greatest number of offspring at risk of perinatal mortality [7-9]. Any congenital anomalies reported on ultrasound will also be recorded.

#### Obstetric Discharge Summary

All neonates born at recruiting maternity hospitals have a standard obstetric discharge summary on discharge from the hospital. Neonatal information collected will include date of birth, gestation at delivery, birthweight, birthweight centile, sex, Apgar’s score, neonatal complications (hypoglycemia, jaundice, congenital anomalies [major/minor], and others). Maternal information will include mode of delivery, and maternal pregnancy complications (GDM, gestational hypertension/preeclampsia, and others).

#### Cheek Swab (for Epigenetic Analysis)

Swabs will be taken from mother and baby using a sterile regular flocked dry swab using a kit supplied at 36 (SD 4) weeks of gestation. These samples will be self-collected by rubbing the swab against the inside of the cheek 10 times and reinserting the swab into the plastic applicator. Samples will be given to nursing staff before discharge. The swabs will be sent to pathology for long-term storage until all samples are collected.

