### Eligibility and Recruitment

#### Inclusion Criteria

Eligibility for the study will be women aged 18 years and older with pregnancies of 20±4 completed weeks of gestation who provide written consent and are attending a prespecified study site for maternity care. The study will include those with multifetal pregnancies, chronic disease, and those using medications of any type. Women from non–English speaking backgrounds will be included and telephone interpreting services and cultural liaison officers will be used as required.

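### Swab kits are supplied only at Visit 2 (36±4 weeks), so women who deliver before that visit have no kit and missing epigenetic samples depend on gestation at birth

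*Protocol article*

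**What the plan says.** The Cheek Swab section of the protocol article says that mother and baby are swabbed "using a kit supplied at 36 (SD 4) weeks of gestation". The samples are self-collected, and "Samples will be given to nursing staff before discharge".

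Table 1 (Clinical Assessments) agrees. The row "Provide maternal and neonatal mouth swabs to participants" has one tick, in the column headed "Visit 2 (36, SD 4 weeks gestation"). The row "Collect maternal and neonatal mouth swabs for epigenetic analysis" is ticked at Visit 2 and at Visit 3 (peripartum). Neither Visit 1 nor Visit 3 has a tick for provision.

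The Recruitment Procedure section places entry well before that visit: "Women will be recruited when they attend maternity care visits between 16 and 24 weeks’ gestation". Secondary Outcomes lists "Offspring born preterm (<37 completed weeks’ gestation") as a component of the neonatal composite. The Data Collection section describes the swab samples as serving to generate hypotheses and keeps them out of the prediction models.

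**The concern.** A newborn can be swabbed only after birth, and under the written schedule the kit must already have been given out at Visit 2. If birth comes first, there is no kit for either mother or baby. The chance of being sampled therefore rises with gestation at birth.

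Gestation at birth is not incidental here, because preterm birth is one of the study's adverse outcomes. The Sample Size section also reasons that most preterm babies will have abnormal growth, which would link the gap to the primary outcome variable. An exploratory methylation comparison by neonatal outcome would then rest mainly on later births. No adjustment could recover births before 32 weeks, since none would be sampled. Multifetal pregnancies are eligible ("The study will include those with multifetal pregnancies"), which may add to the number affected.

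**Working it through.** The article states no sample size or expected yield for the swabs, so there is no figure to reproduce. The check is of the schedule's logic, followed by an illustration of size.

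**Inputs from the article**
- Kit supply: Visit 2 only (Cheek Swab section; Table 1).
- Visit 2 window: 36 − 4 = 32 to 36 + 4 = 40 weeks. This reads SD 4 as ±4. Table 1 labels Visit 1 in the same style, while the eligibility text gives 20±4 and recruitment is at 16 to 24 weeks.
- Participants after dropout: 500 − 25 = 475 (Sample Size).

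**Assumed, not in the article:** the preterm rate, the spread of preterm births and the timing of Visit 2.

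**Rule.** P(no kit | birth at week g) = P(Visit 2 falls after g).
- Birth before 32 weeks: 1.00, whatever the visit timing.
- Visits spread evenly over 32-40 weeks, (40 − g)/8: 0.75 at 34 weeks, 0.50 at 36, 0.25 at 38, and 0 from 40.

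**Illustration A.** Assume 8% preterm (0.08 × 475 = 38 babies), with 15%, 15% and 70% of them born at 31, 33 and 35.5 weeks.
- Visits even over 32-36 weeks: 0.15 + 0.15 × 0.75 + 0.70 × 0.125 = 0.35, about 13 babies.
- Visits even over 32-40 weeks: 0.15 + 0.15 × 0.875 + 0.70 × 0.5625 = 0.675, about 26 babies.
- Visits normal around 36 weeks, SD 1: 0.15 + 0.15 × 0.999 + 0.70 × 0.691 = 0.78, about 30 babies.

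**Illustration B.** Let s be the share of preterm births before 32 weeks, 10-20%. Let the rest fall between 32 and 37 weeks with linearly rising density, so that the fraction born before week v is ((v − 32)/5)². With Visit 2 fixed at week v, the share of preterm babies lost is s + (1 − s) × ((v − 32)/5)².

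| Visit 2 timing | s = 10% | s = 20% |
|---|---|---|
| 32 weeks | 10% | 20% |
| 34 weeks | 0.10 + 0.90 × 0.16 = 24% | 0.20 + 0.80 × 0.16 = 33% |
| 36 weeks | 0.10 + 0.90 × 0.64 = 68% | 0.20 + 0.80 × 0.64 = 71% |
| even over 32-40 weeks | 0.10 + 0.90 × 0.583 = 63% | 0.20 + 0.80 × 0.583 = 67% |

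In the last row, the mean of g − 32 in the 32-37 week group is 5 × 2/3 = 3.33, so the mean chance of no kit is 1 − 3.33/8 = 0.583.

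For comparison, take term births centred on 39.3 weeks (SD 1.2, limited to 37-42). None lacks a kit when Visit 2 is fixed at 36 weeks or earlier, and about 11% do when visits are spread evenly over the window. Preterm loss exceeds term loss in every scenario examined.

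**The part that does not depend on visit timing.** With a preterm rate of 6-12%, there are 28.5 to 57 preterm babies among 475. Births before 32 weeks then number between 28.5 × 0.10 = 2.9 and 57 × 0.20 = 11.4.

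**The case against.** The strongest reply is that no stated analysis is harmed. The swabs are exploratory, the article sets out no epigenetic outcome or comparison, and the neonatal composite does not use them. That stands, and it fixes the point as minor.

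A second reply is that the unseen full protocol or standard operating procedures may let staff hand a kit to a woman who delivers early. That is possible. However, the article is not silent on supply: the text and Table 1 both place it at Visit 2, and Visit 3 is ticked for collection but not for provision. The point is directed at that stated rule.

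A third reply is that issuing kits close to delivery is sensible, since a kit given at 16-24 weeks must be kept for months. That is fair, and it favours a supply at the hospital over relying on Visit 1 alone.

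A reader might infer that preterm babies as a group drop out of the epigenetic samples. The article does not support this. The window opens at 32 weeks, so a preterm baby born after Visit 2 can be sampled. The only certain loss is births before 32 weeks, and the larger percentages depend on visit timing that the article does not give.

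**Conclusion.** The point holds in limited form. Under the written schedule, women who deliver before Visit 2 have no kit, so swab availability depends on gestation at birth. All births before 32 weeks are lost. The further loss at 32-36 weeks is unknown. In total, about 10-20% of preterm babies are lost if Visit 2 is at 32 weeks, and roughly 70-80% if it is near 36 weeks.

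These ranges rest on assumed preterm rates, gestation distributions and visit timing, and on reading SD 4 as ±4. If it were meant as a true standard deviation, some visits could fall before 32 weeks and the loss there would not be complete.

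A reader might also infer bias in the risk calculators or the secondary outcomes. There is none from this source: the swabs do not enter the models, and gestation and birthweight come from the obstetric discharge summary. This is a low-priority improvement to an exploratory collection.

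**What to change.** Add a tick for kit provision at Visit 3 in Table 1, and amend the Cheek Swab section to match. Keep the same kits at the recruiting maternity hospitals for any woman who has not received one. This can reach women already enrolled but not yet delivered, except those who give birth elsewhere.

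Optionally, also issue kits at Visit 1 to women still to be enrolled. At submission 402 of 500 had been recruited, so this reaches at most 500 − 402 = 98 women and cannot be the main remedy.

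For women who have already delivered without a kit, report swab availability by gestation at birth and limit the epigenetic conclusions to the gestations actually sampled.

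The cost is a few extra or lost kits and a small amount of stock-keeping at the hospitals. No outcome, model or sample size changes.
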